### Staged surgical ablation group

Fifty patients will be randomized to surgical ablation of AF. The ablation procedure will be performed with the use of Estech cobra fusion, according to the manufacturer’s instructions and to the commonly described techniques [10,12,15]. Up to three applications will be allowed to ablate the left atrial box. Bidirectional block will be checked, and reasons for not obtaining it will be noted. Inducibility of AF at the end of the procedure will be recorded. Cardioversion will be allowed to restore SR. At the end of the procedure, the patient will be awakened and transferred to the ward. An interval of 3 months will be allowed after the initial ablation procedure, as per the Heart and Rhythm European Society Association/European Heart Rhythm Association/European Cardiac Arrhythmia Society expert consensus statement [13]. During this period, the recurrences of AF, atrial tachycardias, and atrial flutter will not be counted toward the primary or secondary end points. Antiarrhythmic medications may be continued for the first 3 months to avoid early recurrences. At 3 months, they must be stopped to assess recurrences. For patients continuing to have recurrence controlled by the therapy, it will be left to the preference of the investigator to continue the medical therapy or to refer the patient for a PCA.

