### Percutaneous catheter ablation group

One hundred patients will be randomized to PCA and treated according to the protocol of the referring center. In all cases, complete PVI must be at least attempted and confirmed by bidirectional block. The referring investigator can then add any of the current methods of PeAF treatment, including substrate modification with the infusion of isoproterenol to uncover non-PVI triggers and CFAE. Lines can be drawn at the discretion of the investigators. Inducibility of AF at the end of the procedure will be recorded. Cardioversion will be allowed to restore SR.

After the 3-month blanking period, it will be left to the investigator’s preference to refer the patients with PeAF recurrence to a second PCA procedure, surgical ablation, or switch to a rate-control approach. The latter will be counted as a failed repeated procedure.

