### Statistical analysis

Randomization will be performed by using currently available computer software. Sample size is based on the hypothesis that the success rate of the first procedure will be approximately 70% for the surgical cases and 35% to 40% for the PCA cases. At the end of the interventions, the number of patients in SR should be equivalent in the two groups, whereas the proportions of those submitted to a second procedure, either percutaneous or surgical, should differ significantly. Variables will be analyzed with an intention-to-treat method. The three possible results of this study are described in Table 1. A flow chart depicting the most favorable result in which the power of the test is 98% is shown in Figure 1. Data will be expressed as mean ± SD and 95% confidence limits, as appropriate. Comparisons between patient groups will be performed with the Mann–Whitney test for continuous variables and the χ^2^ test for categoric variables. The *z* test and the odds ratio will be used for differences between proportions of patients receiving repeated procedures in the two groups. A value of *P* < 0.05 will be considered statistically significant. Time-to-event distributions will be estimated by the Kaplan-Meier method and compared with the log-rank test. The Cox proportional hazards model will be used to identify independent risk factors for recurrences. Stepwise selection procedure will be adopted. A value of *P* < 0.05 will be considered significant for variable entry for stepwise selection. Analyses are performed with the SPSS 18.0 software package (SPSS, Inc, Chicago, IL, USA).

**Table 1 T1:** Anticipated results for different success rates of first PCA procedure

**% of SR in the PCA group after first procedure**	**35%**	**45%**	**50%**
**χ**^ **2 ** ^**test for first procedure**	*P* < 0.0001	*P* = 0.007	*P* = 0.03
Power of the test	99%	84%	65%

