**Difference between proportions**			
Fraction of second procedures in the two groups	0.65-0.30	0.55-0.30	0.50-0.30
Difference between fractions	0.35	0.25	0.2
95% confidence interval of difference	0.1 to 0.5	0.1 to 0.4	0.0 to 0.3

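### Stepwise Cox selection at P < 0.05 will give the reported risk factors for recurrence inflated hazard ratios, and intervals that ignore the selection

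*Protocol article*

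**What the plan says.** Statistical analysis in the Protocol article fixes the method directly.

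- Aim: "The Cox proportional hazards model will be used to identify independent risk factors for recurrences".
- Route: "Stepwise selection procedure will be adopted".
- Threshold: a P value below 0.05 "will be considered significant for variable entry for stepwise selection".

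The section does not say which variables are candidates, how many there are, or whether the randomised arm is forced in, offered as a candidate or handled elsewhere. It does not label the model exploratory.

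The arms are compared by other means in the same section: the chi-square test, the z test with odds ratio, and the log-rank test. Assessment of recurrence does not list the risk-factor model among the primary or secondary outcomes.

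**The concern.** The same data choose the variables and then estimate their effects. A variable enters only if its estimate happens to be far enough from no effect, so the estimates that survive are biased away from a hazard ratio of 1. The printed intervals and P values are computed as if the final model had been chosen in advance, so they lose their nominal meaning. Each extra candidate also adds another chance for a noise variable to be called an independent risk factor. Readers would take such factors, with their intervals, as established by a randomised trial.

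A second, separate issue is the arm. The entry rule is stated without exception. If the arm is treated like any other candidate, the final model can omit it, and the other hazard ratios are then not adjusted for randomised treatment.

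**Working it through.** **1. Inputs.** Group sizes: "Fifty patients will be randomized to surgical ablation of AF" and "One hundred patients will be randomized to PCA". Rates: "success rate of the first procedure will be approximately 70% for the surgical cases and 35% to 40% for the PCA cases"; Table 1 uses 35%, 45% and 50% for catheter ablation (PCA). Significance level: P "< 0.05 will be considered statistically significant". The number of candidate covariates is not given; I assume a range of 5 to 20, independent and with no true effect.

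**2. The plan's own figure.** The article gives no figure for the Cox model, so Table 1's power is used to confirm the inputs. Two-sided 0.05, pooled variance under the null:

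power = Φ[(|p1 − p2| − 1.96·SE0)/SE1]

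At 70% versus 35%: SE0 = √(0.4667 × 0.5333 × (1/50 + 1/100)) = 0.0864; SE1 = √(0.21/50 + 0.2275/100) = 0.0805; (0.35 − 0.1694)/0.0805 = 2.245, giving 98.8%. The other columns give 83.8% and 65.1%. Table 1 prints 99%, 84% and 65%, so the inputs reproduce.

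**3. Expected events.** Table 1, row "Fraction of second procedures in the two groups", has 0.30 for surgery and 0.65, 0.55 or 0.50 for PCA. Taking these as recurrences after the first procedure: 0.30 × 50 = 15, plus 65, 55 or 50, gives 80, 70 or 65.

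**4. How far an estimate must lie from 1 to enter.** For a covariate in SD units, the standard error of the log hazard ratio is roughly 1/√events. The entry limit is 1.96/√80 = 0.219 (HR 1.25) to 1.96/√65 = 0.243 (HR 1.28), or the reciprocals. A weaker estimate is not reported; a stronger one is. In 2,000 simulated trials per setting, a true HR of 1.25 per SD (log 0.223) averaged 0.350 on the log scale when selected, which is exp(0.350) = 1.42. For pure-noise covariates that were selected, a second simulation (200 to 300 trials per setting) gave a median apparent HR of about 1.3 per SD, in either direction. Their nominal 95% interval covered the true value of 1 in 0% to 0.7% of cases. That is nearly automatic, because entry at P < 0.05 requires the interval to exclude 1.

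**5. Chance of at least one false factor.** With k independent null candidates this is 1 − 0.95^k. The simulated columns are from the second simulation, at PCA success 35% / 50%:

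| k | 1 − 0.95^k | Arm free to enter | Arm forced in |
|---|---|---|---|
| 5 | 22.6% | 24% / 22% | 19% / 27% |
| 10 | 40.1% | 41% / 43% | 40% / 43% |
| 15 | 53.7% | 59% / 59% | 63% / 53% |
| 20 | 64.2% | not run | not run |

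Monte Carlo error is about 2 to 4 points. The larger simulation gave 41% / 41% at k = 10 and 56% / 53% at k = 15. Forcing the arm in makes no consistent difference.

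**6. The arm as a mere candidate.** With constant hazards, Table 1 implies HR = ln 0.70/ln 0.35 = 0.34 and ln 0.70/ln 0.50 = 0.51. At 35% PCA success the arm entered in about 98% to 99% of trials or more, so it was missing in about 1% to 2%. At 50% it entered in 61% to 64% in the larger simulation and 63% to 70% in the smaller, so it was missing in about 30% to 39%.

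**The case against.** The strongest reply has four parts.

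- **The article is condensed.** Candidate lists and forced terms are commonly left to a fuller document. This stands for those details, and their absence is not the point here. It does not cover the selection rule, which the article states.
- **The analysis is supporting.** It is not a listed outcome. This stands and limits the importance.
- **The fix hardly lowers the false-positive count.** A fixed model with 5 to 7 null covariates would still show at least one P < 0.05 in 1 − 0.95^5 = 23% to 1 − 0.95^7 = 30% of trials. This stands. The gain is intervals that mean what they say, with every tested factor visible.
- **Losing the arm is unlikely at the planned rates.** The sample size rests on 35% to 40% PCA success, and at 35% the arm almost always enters. This stands; the 30% to 39% figure belongs to Table 1's least favourable column.

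A reader might also infer stronger claims that the documents do not support. The article does not say that the arm is left out. Leaving it out would not be the cause of false factors, as the table shows. Nor would it confound the baseline covariates, which are independent of a randomised arm in expectation; at most their hazard ratios would be attenuated. The treatment comparison does not hang on this model. Finally, the Discussion's hope of refining techniques and devices is attached to the staged design, not to the Cox analysis.

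**Conclusion.** The stated selection method is a poor choice and should be changed. Hazard ratios of selected variables will be exaggerated, and their intervals and P values cannot be read at face value. This follows from the rule itself and does not depend on the number of candidates. The chance of at least one false factor does depend on it, from about 23% to 64% over the assumed range of 5 to 20 independent null candidates. Whether false factors would be frequent therefore cannot be settled from the article.

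The arm is a separate and conditional matter: it arises only if the arm is treated as an ordinary candidate, and it is material only if PCA success is well above the planned 35% to 40%.

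The figures assume that the modelled event is recurrence after the first procedure, that event times are exponential, and that Table 1's rates apply. The chi-square, z and log-rank comparisons, the sample size and the power are untouched.

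**What to change.** Replace the two sentences on stepwise selection with a statement along these lines: recurrence will be analysed in one Cox model containing the randomised arm and a short list of baseline covariates named before the data are examined; all hazard ratios will be reported with 95% confidence intervals, whatever their P values; any further data-driven screening will be labelled exploratory.

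The investigators should choose the covariates and size the list to the expected events. As an illustration, 6 to 8 terms including the arm would leave between 65/8 ≈ 8 and 80/6 ≈ 13 events per term. That cap is a judgement and does not come from the article.

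The cost is a sentence of text and fewer candidate factors examined. The change restores the meaning of the intervals and guarantees adjustment for treatment. It does not remove multiplicity across the covariates, so an isolated P < 0.05 among them should still be read with caution.

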**Strength of association**			
Relative risk	2.2	1.8	1.66
95% confidence interval	1.4 to 3.4	1.2 to 2.9	1.0 to 2.6
Odds ratio	4.3	2.9	2.33
95% confidence interval	2.1 to 9.0	1.4 to 5.9	1.1 to 4.7
**Difference between proportions**			
Fraction of second procedures in the two groups	0.65-0.30	0.55-0.30	0.50-0.30
Difference between fractions	0.35	0.25	0.2
95% confidence interval of difference	0.1 to 0.5	0.1 to 0.4	0.0 to 0.3

**Figure 1 F1:**
[figure not shown]
Flow chart of the study.

## Discussion

PeAf is more complex to treat than the simple paroxysmal AF. Several different percutaneous and surgical techniques have been proposed for its treatment, owing to the difficulties in the standardization of the ablation procedures. In addition, many reports dealing with the ablation of PeAF also include patients affected by paroxysmal and permanent fibrillation, which introduces a considerable selection bias.

As in any arrhythmia, a number of basic problems are involved in ablating the PeAF, including the following: (a) identifying the mechanism; (b) locating the source; (c) reaching the ablation area; (d) choosing the lesion set; and (e) consistently obtaining transmural lesions. As PeAf shows heterogeneity in its mechanism of origin, a simple PVI has unpredictable results. Thus, other techniques such as CFAE ablation and linear ablations, with or without substrate control, have been developed to increase the percentages of termination of the arrhythmia. Once the arrhythmia has been ablated, it can also recur in other parts of the atrium with a different mechanism, causing a high percentage of recurrent fibrillation. Recently, focal ablation and the rotor modulation technique (FIRM) [16] have shown promising results in a limited number of cases. Surgical ablations that de-connect a large part of the posterior left atrium, where many of the sources of the PeAF are located, have also become increasing used owing to their simple approach. Conversely, surgical procedures also are difficult to evaluate, and numerous observational studies of mixed populations without controls used different sources of energy and line combinations [15,17,18].

The FAST trial [7] was the first to compare the surgical and the percutaneous approaches, in which patients randomized to surgery had a higher rate of termination of the arrhythmia. However, their results were compromised by the incidence of complications. Many of these complications (pneumothorax, rib fracture) could be easily avoided by careful analysis of the results and by experience, which eventually results in an equivalent rate of complications between the two experiment groups. Further, the surgical ablation in that study was performed through a bilateral minimal thoracotomy. This approach was necessary to accomplish a complete surgical PVI with the use of bipolar radiofrequency delivered by the Atricure device. The bilateral approach adds time and increases the chances of complications. This can be avoided with different devices such as the Estech Cobra Fusion, which is capable of a complete electrical deconnection of the posterior left atrium, delivering bipolar radiofrequency through a single right minimally invasive approach. According to the European Guidelines [12], bipolar radiofrequency is the preferred source of energy for achieving a complete transmural line of ablation [19]. The transmurality of the lesions can be consistently obtained with hybrid or simultaneous [9] and staged or sequential [10] approaches.

The hybrid simultaneous procedures have some disadvantages, in that they take time and do not allow a blank period to evaluate the clinical efficacy of surgery. The staged procedures allow a blank period of evaluation, and two modalities of ablation (surgical and percutaneous) may be used after a predetermined period or only in case of recurrences.

All of these procedures share the same basic principles. The posterior left atrium (the portion where many of the sources of PeAf are located) must be electrically separated from the base of the heart [8], with the addition of some endocardial lines, if necessary. In our study, we have chosen to adopt a staged approach. This has some possible advantages, including the evaluation of the efficacy of a monolateral minimally invasive approach by using bipolar radiofrequency. For this, we will use the Estech Cobra Fusion system. The ablation device encircles the posterior portion of the left atrium and allows the use of bipolar radiofrequency in a controlled protocol. Second, the procedural time is expected to be relatively short so as to avoid any ICU stay. Third, a blank period will allow a second percutaneous ablation to be performed only in patients with recurrent AF, which should reduce the total number of invasive procedures necessary to control the AF.

Finally, in our opinion, this will allow us to study the modalities of failures of the surgical approach and give valuable information in refinement of the techniques and devices.

### Study limitations

No standard strategy is known for the percutaneous ablation of PeAF. In the PCA control group of our study, the choice of the initial technique will be left to the treating cardiologist (PVI, CFAE ablation with or without manipulation of the substrate, or rotor manipulation are frequently used in combination or in staged procedures). Insulated PVI is the least effective technique, whereas rotor modulation has been recently introduced and is not widely used. Thus, we expect that the majority of the patients in the control group will undergo a combination of PVI and CFAE ablation. In cases of failure in the surgical group, this choice will be dictated by the residual electrophysiological findings. This is a potential limitation of the study that may make comparison between the two groups difficult.

## Trial status

At the moment of submission, the trial is recruiting patients.

## Abbreviations

AF: Atrial fibrillation; CFAE: complex fractioned atrial electrogram; ECAS: European Cardiac Arrhythmias Society; ECG: electrocardiogram; EHRA: European Hearth Rhythm Association; FAST: atrial fibrillation catheter ablation versus surgical ablation treatment; HRS: Heart Rhythm Society; LMW: low molecular weight; PCA: percutaneous catheter ablation; PeAF: persistent atrial fibrillation; PVI: pulmonary vein insulation; SR: sinus rhythm; TEE: transesophageal echo; PAF: paroxysmal atrial fibrillation; SSA: staged surgical ablation.
